**Table 3 Tab2:** **Quality indicator set for cardiac rehabilitation per study arm**

**Study arm**	**Nr**	**Type**	**Quality indicator**
A	1	Structure	Specialized education for patients with chronic heart failure
	2a	Process	Complete data collection during needs assessment for rehabilitation (concerning psychological and social functioning, and lifestyle factors)
(Patient education, quality of life, and lifestyle change therapy [ex. physical activity])			
	3	Process	Patients receive a discharge letter to stimulate continuation of lifestyle changes at home
	4	Outcome	Patients quit smoking
	5	Outcome	Patients improved their quality of life during rehabilitation
B	2b	Process	Complete data collection during needs assessment for rehabilitation (concerning physical functioning and, cardiovascular risk factors)
(Exercise training and physical activity, relaxation and stress management, cardiovascular risk factors, and work resumption)			
	6	Process	Cardiovascular risk factors are evaluated after rehabilitation
	7	Outcome	Patients improve their exercise capacity during rehabilitation
	8	Outcome	Patients meet the physical activity norms
	9	Outcome	Amount of time needed to start resumption of work
A and B	10	Structure	Rehab professionals work with a multidisciplinary patient record
	11	Structure	Long-term patient outcomes are assessed
	12	Structure	Patients participate in patient satisfaction research
	13	Structure	Clinics perform internal evaluations and quality improvement
	14	Process	Average time between hospital discharge and start of rehabilitation
	15	Process	Patients are offered a rehabilitation program tailored to their needs
	16	Process	Patients finish their rehabilitation program
	17	Process	Rehabilitation goals are evaluated afterwards
	18	Process	Cardiologists receive a report after the rehabilitation

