### Intervention

We will carry out a multifaceted guideline implementation intervention that consists of two elements: (i) quarterly feedback on quality indicators for CR, provided as part of a web-based QI system and (ii) educational outreach visits using the same system to set up a QI plan together with a local QI team. Table 2 gives an overview of the complete intervention for both study arms.i.)Feedback. Each 3 months, all participating clinics will receive feedback on a set of quality indicators for CR [24], based on data that are recorded by the CDS system. Feedback reports will be presented within the web-based QI system called CARDSS Online, which was specifically developed for this study [39]. Within this system, clinics can monitor their performance on the quality indicators listed in Table 3. Figure 3 shows a screenshot from the feedback report page in CARDSS Online. After clicking on an indicator button, a pop-up screen opens with detailed information about data underlying the calculation, national averages for comparison, and benchmark values. Feedback will be attuned to the research arm concerned: clinics allocated in arm A will receive feedback on quality indicators referring to psychosocial domain; clinics allocated in arm B will receive feedback on indicators referring to the physical domain. Both arms will receive feedback on indicators referring to general processes and structures (see Table 3).To assist the QI teams with selecting the quality indicators requiring improvement, a colored icon next to each indicator score indicates whether the performance is acceptable (green checkmark), borderline (orange checkmark), or poor (red exclamation mark). In addition, results will be compared to statistics from the same clinic during earlier periods to quantify change. When a clinic’s average for a given indicator is poor or differs (both in positive and negative sense) from previous results, this will be discussed during the outreach visits. Icon colors are automatically determined by the CARDSS Online system, using predefined rules (see Appendix I).ii.)Outreach visits*.* Feedback reports will be received by all participating clinics on a 3-month basis and followed by outreach visits to support interpretation of the report and to draft a QI plan. This approach was chosen to match the conclusion from the Cochrane review that the feedback may be more effective when it includes both an action plan and explicit goals [17]. During development of the QI plan content, additionally, the goal-setting theory, stating that feedback and well-specified goals are indeed a successful combination, was used. The theory emphasizes that people tend to be more committed to attaining a certain goal if they are involved in setting it, if (the outcome of) goal attainment is seen as important, and if people believe they are capable of accomplishing it [40]. To this end, each clinic needs to set up a local QI team with the responsibility to define, implement, and monitor a QI plan including concrete QI goals based on self-identified issues in the feedback reports.QI team: Setting up a QI team implies the allocation of at least two CR team members for an average of 3 h per month (anyhow, the nurse acting as rehabilitation coordinator and one person from another discipline) and two members for an average of 1 h per month (a cardiologist and a representative from the management) during the study.QI plan: The QI team can use CARDSS Online to grade indicators that the team aims to improve based on importance (five categories), feasibility (five categories), and expected time needed (three categories). CARDSS Online then ranks the indicators based on assigned ratings, and the team can select indicators for final inclusion in the QI plan. In principle, all quality indicators can be selected for improvement, but teams are encouraged to focus on a small subset of three to four indicators during each 3-month cycle. For each quality indicator included in the QI plan, users can specify the problem, presumed causes, improvement goal, and concrete actions on how to reach that goal. CARDDS Online does not provide tools, other than documentation, for systematic problem analysis or suggestions for improvement actions. For each action, the names of responsible team members and a deadline for achievement has to be entered.

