### Outcome measures

As in most guideline implementation studies, the proposed intervention is targeted at health care providers and is therefore expected to have a direct effect on process outcomes and to have only indirect, long-term effects on patient outcomes. The primary outcome measure will therefore be concordance, at patient level, to national CR guidelines with respect to the needs assessment (concordance of clinical decisions with the guidelines, for four group-based therapies). We will measure whether patients are treated according to the recommendations of the guidelines (i.e., treating patients who should have been treated and not treating patients who should have been untreated).

Secondary outcome measures are changes in performance of participating clinics as measured by 18 quality indicators for CR (see Table 3) and changes in practice variation on these indicators. Table 1 describes how the indicator set was developed [24].

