### Statistical analysis

For the primary outcome measures, we will use mixed-effect logistic regression analysis [7,58], including clinic as random effect, to assess the effect of the intervention. Included covariates will be study arm, time since study start, and time × arm interaction. We will focus on the interaction term to assess the difference in change over the study period between the two arms—that is, the effect of the intervention—because we expect concordance to improve gradually.

For the secondary outcome measures, a similar analysis will be conducted, though replacing the logistic function by another link function as appropriate. Changes in practice variation will be assessed by including a random coefficient for ‘time since study start’ in the regression model and comparing the variation in estimated quality scores before and after the study.

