Our study design also has some limitations. First, only CR clinics that use an EPR with CDS that facilitates registration of our minimal dataset are eligible to participate. Second, these clinics should be willing to dispose their data for research and to allocate resources to set up a QI team (volunteer bias). These two criteria may lead to the selection of a non-representative sample of CR clinics because eligible clinics are less likely to be understaffed and more likely to have information technology support to facilitate routine collection of CR data. The generalizability of our results will thus be limited to CR clinics that are motivated and equipped to systematically monitor and improve the quality of care they deliver. The essence of our intervention is that QI teams are free to formulate any improvement action, including those not specifically targeted at improving concordance to a specific guideline recommendation. Although this maximizes the involvement of the team in the improvement process and the commitment to goal attainment, it weakens the link between our intervention and primary outcome measure. By measuring changes in performance on the entire set of quality indicators as a secondary outcome, we aim to assess the direct relation between our intervention and performance changes. However, as is common in guideline implementation studies, these performance changes will only have indirect, long-term effects on patient outcomes. Fourth, the block randomization might cause underestimation of the effect size as clinics might start to improve both CR domains and not just the domain covered in their study arm because the intervention has raised their awareness for QI. Finally, the feedback on quality indicators will not automatically be corrected for differences in patient mix. However, during the trial, participating clinics can always request additional analyses on their data like, e.g., correction for patient mix to interpret their quality indicator results.

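### Nine of the 18 secondary indicators are fed back in both arms, so the planned time × arm contrast does not estimate the intervention's effect on them

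*Protocol article*

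**What the plan says.** All places are in the protocol article.

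- **Outcome measures:** the secondary outcomes are "changes in performance of participating clinics as measured by 18 quality indicators for CR", together with changes in practice variation on the same indicators.
- **Intervention:** clinics receive feedback on the indicators of their own domain (arm A psychosocial, arm B physical). In addition, "Both arms will receive feedback on indicators referring to general processes and structures (see Table 3".
- **Table 3:** the block labelled for both arms runs from number 10, "Rehab professionals work with a multidisciplinary patient record", to number 18, "Cardiologists receive a report after the rehabilitation".
- **Statistical analysis, primary outcome:** mixed-effect logistic regression with a random effect for clinic. "Included covariates will be study arm, time since study start, and time × arm interaction". The interaction is identified as the effect of the intervention.
- **Statistical analysis, secondary outcomes:** "For the secondary outcome measures, a similar analysis will be conducted, though replacing the logistic function by another link function as appropriate". No separate rule is given for indicators shared by the arms.
- **Study design** and **Study aim and hypothesis:** each arm is the other's control, and the comparator is the electronic record with decision support alone.
- **Strengths and limitations:** the authors concede a weak link between intervention and primary outcome, and continue: "By measuring changes in performance on the entire set of quality indicators as a secondary outcome, we aim to assess the direct relation" between the intervention and changes in performance.

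**The concern.** The design obtains a control group by giving each arm the intervention for one domain only. That works for an indicator fed back in one arm. It does not work for an indicator deliberately fed back in both, because neither arm then shows what happens under decision support alone. The analysis paragraph nevertheless extends the same between-arm contrast to the secondary outcomes without distinguishing the two kinds of indicator.

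The loss falls where the article expects the intervention to act. Outcome measures anticipates a direct effect on process and only indirect, long-term effects on patient outcomes. The shared indicators are all structure or process indicators. The limitations mention unintended spill-over from one domain to the other, but not the indicators that both arms receive by design. A null interaction on a shared indicator could then be mistaken for evidence that the intervention does not work, and a non-null one for evidence that it does.

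**Working it through.** **1. Count from Table 3**

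| Exposed arm | Indicators | Count |
|---|---|---|
| A only | 1, 3, 4, 5 | 4 |
| B only | 6, 7, 8, 9 | 4 |
| Split by content | 2 (2a in A, 2b in B) | 1 |
| A and B | 10 to 18 | 9 |
| Total | | 18 |

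The article's figure of 18 is reproduced. Counting 2a and 2b as one, the shared indicators by type are:

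- structure: 4 of 5 (10 to 13);
- process: 5 of 8 (14 to 18);
- outcome: 0 of 5.

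So 9 of 5 + 8 = 13 structure and process indicators are shared. Each clinic receives feedback on 5 + 9 = 14 indicators, 9 of them shared.

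**2. What the interaction estimates**

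On the link scale, let s be the secular slope common to both arms, and b_A and b_B the change in slope that the intervention causes in an exposed arm. With the interaction coded A minus B:

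- exposed in A only: (s + b_A) − s = b_A, apart from spill-over;
- exposed in B only: s − (s + b_B) = −b_B, apart from spill-over;
- exposed in both: (s + b_A) − (s + b_B) = b_A − b_B.

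In the shared case the result is 0 when b_A = b_B, whatever their common size. When they differ, it is a difference between two exposed arms. The average slope over both arms is s + (b_A + b_B)/2. It contains the effect, but cannot be separated from s without an unexposed group.

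**3. Illustration by simulation**

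Inputs from the article: 18 clinics (Abstract; the Sample size section aims for at least 19), 350 patients per clinic over one year, ICC 0.063, alpha 5%. The article gives no effect size for indicators 10 to 18, so the rise from 59.6% to 74.6% is borrowed from relaxation therapy in the Sample size section:

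ln(0.746/0.254) − ln(0.596/0.404) = 0.689 on the logit scale.

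Assumptions: 9 clinics per arm, ICC on the latent scale, a two-sided test, no secular trend, and a between-clinic slope SD of 0 or 0.4. Clinic-level logit slopes were compared between arms by t-test, a simpler stand-in for the mixed model, with 3,000 runs per scenario.

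| Scenario | Mean interaction (SD 0 / SD 0.4) | Rejection rate (SD 0 / SD 0.4) |
|---|---|---|
| One arm exposed | 0.689 / 0.690 | 0.949 / 0.707 |
| Both exposed, equal response | −0.001 / −0.002 | 0.056 / 0.049 |
| Both exposed, second arm at 75% | 0.171 / 0.172 | 0.147 / 0.090 |
| Both exposed, second arm at 50% | 0.341 / 0.353 | 0.443 / 0.252 |

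In the last two rows the intervention raises the slope by 0.689 in one arm and by 0.517 or 0.344 in the other. The interaction recovers neither value, only about the differences 0.172 and 0.344. The rejection rates depend on the assumed effect and slope SD. The zero expectation under equal response does not.

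**The case against.** The strongest defence is that the article commits to less than this. The sentence singling out the interaction stands in the paragraph on the primary outcome, and its reason (gradual improvement in concordance) is specific to that outcome. For the secondary outcomes the article promises only a similar analysis of changes in performance. The planned model contains a time term, so a common change can be read from it, and an analysis plan that is not shown may say which coefficient is read for which indicator.

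Part of this stands: the model can produce the common change. But the only modification stated for the secondary outcomes is the link function. The time term is never named as the effect for shared indicators, and what it gives is uncontrolled. The point is not that detail is missing. A definition of effect that is valid for one set of indicators is extended to another set where it is not.

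A reader might infer something stronger: that the analysis will show no effect on these nine whatever the intervention does, or that power equals alpha at any effect size. The documents do not support that. Both statements need equal response in the two arms. Teams choose which indicators to work on and are encouraged to take three to four per cycle, and the shared indicators compete with different domain indicators in A and B, so uptake may differ. A chance rejection also remains possible. Nor does the article say that a null interaction on a shared indicator would be reported as lack of effect; that is a risk, not a stated plan. Finally, the Discussion sentence on the entire set expresses an aim and does not claim a randomised control for every indicator.

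**Conclusion.** The point holds in conditional form. For 9 of 18 secondary indicators the planned interaction contrasts two exposed arms, which does not fit the article's own statements that the arms control each other and that the comparator is decision support alone. Under equal response the contrast has expectation zero and rejects at about the 5% level (0.056 and 0.049 in the simulation, despite an assumed 15-point improvement in both arms). Under unequal response it answers a different question. The count and the algebra rest on the text alone; the simulated rates rest on the assumptions listed in the working.

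The scope is limited. The primary outcome and the arm-specific indicators keep their controlled comparison. The practice-variation analysis is a before-after comparison, itself uncontrolled, to which the interaction argument does not apply. This should be fixed because it changes what the trial can conclude on half of its secondary indicators, but it does not threaten the main result.

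**What to change.** 1. In Statistical analysis, limit the time × arm estimate of intervention effect to the arm-specific indicators and name the exposed arm: 1, 2a, 3, 4 and 5 in arm A; 2b, 6, 7, 8 and 9 in arm B.
2. For indicators 10 to 18, state that the common change over time across both arms will be reported, labelled as uncontrolled and without a causal claim.
3. In Strengths and limitations, amend the sentence on the entire indicator set so that it is not presented as a controlled test of the intervention.

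The change is to wording only: no new data, and no change to randomisation, sample size or the primary analysis. The price is that the randomised causal claim is given up for nine secondary indicators, a claim that the design cannot support for them in any case.

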## Methods

### Study design

The effect of the intervention will be evaluated in a multicenter cluster-randomized study with a balanced (2 × 2) incomplete block design. Cluster-randomization is chosen to avoid contamination among professionals within the same clinic [25]. During the trial, clinics will be divided into two study arms (A and B). Using the multidisciplinary character of CR treatment, each arm will receive the intervention (a web-based QI system with feedback and educational outreach visits) directed at one out of the two domains described in the CR guidelines [26]. Clinics allocated in arm A will receive the intervention directed at improving guideline concordance for the psychosocial domain, clinics in arm B for the physical domain (see Figure 2 for an overview of the study flow). In this way, both study arms will serve as each other’s control. For all participating clinics, the study period is 1 year.

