### Sample size

To calculate the minimally required number of CR clinics participating in the trial, data from a previous trial (concerning the effect of CDS on guideline concordance) was used [7]. Calculations were based on the normal approximation to the binomial distribution, using a type I error risk (alpha) of 5% and 80% power. Also, we assumed that participating clinics will see 350 CR patients, on average, during the study period of 1 year, and that there will be a design effect of 23.0 due to clustering. This is based on an intra-cluster correlation coefficient (ICC) of 0.063, which is the median ICC for process variables found in 21 studies, reported by Campbell et al. [57].

In the previous study [7], CDS increased concordance with guideline-recommended therapeutic decisions for exercise training from 84.7% to 92.6%. To demonstrate a further increase to 97.6% (+5%) in the current study, at least 19 participating clinics (6,712 patients) are required under the assumptions given. For education, the concordance level previously rose from 63.9% to 87.6%. Demonstrating a further increase to 95.1% (+7.5%) requires 14 participating clinics (5,057 patients). For relaxation therapy, the previous study showed an increase from 34.1% to 59.6%, and showing an additional increase to 74.6% (+15%) requires ten participating clinics (3,517 patients). For lifestyle change therapy, finally, no significant effect of CDS was observed in the previous study (57.4% vs. 54.1%). To prove that the current intervention causes an increase from 57.4% to 72.4% (+15%) will also require that 13 clinics (3,632 patients) participate. Based on these results, we aim to include at least 19 CR clinics in our study.

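### Change in practice variation is assessed by a before-after comparison with no between-arm contrast and no stated scale, so a fall in spread cannot be separated from a secular trend

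*Protocol article*

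**What the plan says.** The Outcome measures section lists, as part of the secondary outcome, "changes in practice variation on these indicators", meaning the 18 quality indicators of Table 3.

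The Statistical analysis section sets out three things:
- For the primary outcome, a mixed-effects logistic model with clinic as random effect: "Included covariates will be study arm, time since study start, and time × arm interaction". The interaction is read as the intervention effect.
- For the secondary outcomes: "For the secondary outcome measures, a similar analysis will be conducted, though replacing the logistic function by another link function as appropriate".
- For variation, a separate method: "Changes in practice variation will be assessed by including a random coefficient" for time, followed by "comparing the variation in estimated quality scores before and after the study".

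Two design features matter here. Under Study design, "both study arms will serve as each other’s control", because arm A receives the intervention for the psychosocial domain and arm B for the physical domain. Under Intervention, "Both arms will receive feedback on indicators referring to general processes and structures". Table 3 lists these shared indicators as numbers 10 to 18, which is 9 of the 18.

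**The concern.** The design provides a concurrent randomised control for each arm-specific indicator, but the contrast stated for variation runs over calendar time only. Anything that brings clinics closer together during the study year would be counted in full. The article names a plausible cause: its section on potential implications reports that the national inspectorate recently asked cardiac rehabilitation clinics to improve, after a quality assessment of all of them. Such pressure could lift the weakest clinics in both arms.

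The second issue is the scale on which spread is measured. The article does not fix it. Its own description of practice variation (Table 1, study I) is in percentages, and on that scale spread is tied to the mean. An indicator that moves towards 100% will show less spread even if clinics differ on the logit scale exactly as before.

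Persisting variation between clinics is part of the trial's rationale, so a reader will want to know whether the intervention reduced it. The stated comparison cannot answer that.

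**Working it through.** The article gives no figure for practice variation, so there is nothing to reproduce. The check has two parts.

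**1. Does any stated term compare spread between arms?**

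Write the link-scale model for clinic j at time t as fixed effects (arm, time, time × arm) + b0j + b1j·t, where b0j and b1j are the random intercept and slope. The between-clinic variance at time t is

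s0² + 2·t·s01 + t²·s1².

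The time × arm coefficient does not appear in it. With one covariance matrix for both arms, and none other is stated, the modelled change in link-scale variance is the same in both arms by construction. The variance can move either way, whatever the mean does. With assumed values s0 = 0.47, s1 = 0.3 and t = 1, it goes from 0.221 to 0.311, 0.226 or 0.142 for an intercept-slope correlation of 0, −0.3 or −0.6. The model can therefore describe a change in spread, but as stated it cannot attribute the change to an arm.

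**2. How much does percentage-scale spread move when only the mean moves?**

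Inputs:
- The "intra-cluster correlation coefficient (ICC) of 0.063" from Sample size, read here as a latent-scale ICC (an assumption).
- The four pairs of planning means in the same section. They belong to therapy concordance, not to the 18 indicators, and serve only as illustrations.
- Lower starting means, which are assumed.

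Logit SD: s² = 0.063 × (π²/3) / (1 − 0.063) = 0.063 × 3.290 / 0.937 = 0.221, so s = 0.47.

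Model: logit(pj) = μ + s·uj, with uj standard normal. For each mean, μ is solved so that the average of pj equals it. The SD of pj is then computed by Gauss-Hermite quadrature, with s unchanged between start and end.

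| Mean moves from → to | SD before (points) | SD after (points) | Change |
|---|---|---|---|
| 92.6% → 97.6% (exercise training) | 3.29 | 1.15 | −65% |
| 87.6% → 95.1% (education) | 5.12 | 2.26 | −56% |
| 59.6% → 74.6% (relaxation) | 10.79 | 8.65 | −20% |
| 57.4% → 72.4% (lifestyle change) | 10.95 | 9.09 | −17% |
| 45% → 60% (assumed) | 11.07 | 10.76 | −3% |
| 40% → 55% (assumed) | 10.76 | 11.07 | +3% |
| 30% → 45% (assumed) | 9.52 | 11.07 | +16% |
| 20% → 35% (assumed) | 7.39 | 10.25 | +39% |

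Hand check: SD ≈ s·p(1 − p), so the ratio after/before is close to the ratio of p(1 − p). For exercise training this is (0.976 × 0.024) / (0.926 × 0.074) = 0.0234 / 0.0685 = 0.34, a fall of about 66%.

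Sensitivity: with a logit SD of 0.7 or 1.0, every sign is the same. The fall for exercise training is 64% or 62%, for lifestyle change 16% or 15%, and the rise for 20% → 35% is 36% or 32%. Reading the ICC on the proportion scale instead roughly doubles the absolute SDs (exercise training 6.6 → 2.5 points) but leaves the relative falls almost the same: 62%, 54%, 20% and 17%.

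On the logit scale the change is zero by construction. Under an identity link, a uniform shift leaves the SD unchanged.

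**The case against.** The other side has a fair case on several points.

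- **Spread does not fall whenever the mean rises.** A reader might infer that the method always shows shrinking variation as performance improves. The table refutes this: spread rises from low means and barely moves when the rise straddles 50%. The article does not commit to the percentage scale, and its models are fitted on a link scale. Some indicators are times or other numeric measures. The five structure indicators (1 and 10 to 13) are scored yes or no per clinic, so a patient-level model does not apply to them.
- **Shrinkage is not established.** A reader might also infer that shrunken clinic predictions will be compared, so that the result depends on patient numbers per period. The wording fits model-implied variances at start and end equally well. A random-slope model fitted to the whole year uses all of a clinic's patients for both ends, so reliabilities computed per period would not describe it.
- **No causal claim is announced.** The article ties the intervention effect to the time × arm term and calls this outcome a change in variation. It does not say that a fall will be credited to the intervention.
- **Percentages may be the right scale for practice.** If all clinics approach 97%, patients do meet less variation. That is so, but this fall adds nothing to what the rise in the mean already shows.
- **An article condenses.** Scale and test may be set out in an analysis plan that is not shown.

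These points limit the claim about scale. They do not remove the main one. The before-after contrast is stated, not omitted, and it has no arm in it. The reference to a similar analysis does not supply one, because variation is then given its own method.

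**Conclusion.** The point holds in this form. The stated comparison for practice variation leaves the available randomised control unused for the arm-specific indicators, so a fall in spread could not be told from a secular trend. That follows from the text alone and needs no assumption.

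The scale issue is conditional. If spread is compared in percentage points, a rise in means above about 50% reduces it mechanically, illustratively by 17% to 65%. This rests on constant logit-scale heterogeneity, normally distributed clinic effects, and means and an ICC borrowed from the planning of the primary outcome. The article gives no baseline or ICC for the 18 indicators, so the size for any one of them is unknown.

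For indicators 10 to 18 no analysis can supply a randomised contrast, because both arms receive the feedback. The primary analysis is unaffected.

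**What to change.** Amend the sentence on practice variation as follows:

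1. State the scale. Use the between-clinic variance from the model on the link scale, at study start and end, and say that it is a variance component and not the spread of predicted clinic scores.
2. For the arm-specific patient-level indicators (2a and 3 to 5 for arm A; 2b and 6 to 9 for arm B), let the random intercept and slope covariance differ by arm. Compare the start-to-end change in variance between the exposed and unexposed arms and report it with its interval, for example from a parametric bootstrap. Percentage-point spread can be shown alongside as description.
3. Report the change in variation for indicators 10 to 18 as uncontrolled and descriptive. Tabulate the yes/no structure indicators, including indicator 1, by arm.

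No new data are needed, since the minimal dataset in the Participants section covers all 18 indicators in every clinic. The cost is a few extra variance parameters and low precision. With the 18 clinics of the Abstract, about nine per arm (18 / 2), the intervals will be wide and some models may have to be simplified. The report should show that imprecision; it is not a reason to drop the control.
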